##### Dates and Times

Records on the date and time of events in routine data require consideration. With most events recorded by day, we are obliged to use day as the primary measure of time, and therefore collisions will occur.

In EDDS the date and time of attendance and discharge are recorded, and several events can occur on the same day. For example, it is feasible that a patient attends ED on multiple occasions and on the same day. ED attendances on the same day are collapsed onto one another under the superspell assumption. In the WDSD, while date of birth is approximated to the Monday of the week in which they were born (their Week of Birth), date of death is accurate to that degree of granularity.

For example, a patient might attend ED at 9 AM and die at 2 PM on the same day. To avoid inconsistencies such as this patient entering the study cohort after death, we will adopt the usual approach and add a small value (ε) to dates to preserve the chronological order of events [52].

##### Matching

It is not possible to manipulate allocation to treatment, and we therefore rely on quasi-experimental methods to infer treatment effects. The purpose of matching control and intervention patients is to allow derivation of the average treatment effect under the assumption that allocation is not conditional on observed confounders. Matching on values of covariates between the treated and untreated groups avoids the bias introduced by covariates that influence the outcome variable. The goal being to find a subset of data that is closest to an exact match on observed covariates [53]. The primary analysis will be conducted using coarsened exact matching, with a minimum 1:1 ratio, with secondary analyses undertaken using propensity score matching.

For categorical covariates, exact matching is a sensible alternative. Here a match is considered acceptable only if the values of all covariates are equal between treated and untreated potential matches. Continuous covariates can, for the purpose of using exact matching, be turned into categorical covariates by defining category intervals; the resulting method is called coarsened exact matching. For matching, covariate categories can be grouped together to form larger (and fewer) categories, improving efficiency [53-55]. This approximates to a fully blocked experiment and requires temporarily coarsening variables.

Propensity score matching reduces the multidimensional space of covariates to a single summary covariate, the propensity score, typically derived using a logistic equation and performing regression on the treatment group for the covariates chosen to match with. The proximity of a potential match to the given subject is estimated in terms of the closeness of their propensity scores. This method simplifies subsequent analyses, as matching refers only to one variate, the propensity score. However, propensity score matching can increase, rather than decrease, the imbalance of the covariates in the samples [53]. A challenge is optimizing the trade-off between the quality of matches and the sample size. A larger sample reduces sampling error and can increase the study power, but including matches of lower quality may lead to greater residual imbalance [56]. The R package Matching Frontier attempts to address these issues by calculating the entire balance-sample size frontier, from which the user can easily choose one, several, or all subsamples to use for their final analysis, given their own choice of imbalance metric and quantity of interest [57,58].

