**Methods:**

ED patients are eligible for inclusion in the evaluation if they are normally resident in Wales, United Kingdom, aged 11 years and older. A controlled longitudinal natural experiment will be undertaken. The primary outcome is derived from the Emergency Department Dataset, routinely collected for all EDs in Wales, and is subsequent unplanned ED attendance. Case patients will be matched to control patients attending EDs without an HVIP. Analysis will derive the hazard rate for subsequent unplanned ED attendances using recurrent event analysis. The total monthly count of patients identified as attending because of violence in intervention EDs will be compared to the total count of Welsh control EDs in an interrupted time-series analysis to determine whether HVIPS increase violence ascertainment. To determine whether referral, versus no referral, to the HVIP represents value for money, we will undertake a cost-effectiveness analysis from the perspective of the National Health Service. The approval to access and analyze data housed in the Secure Anonymized Information Linkage (SAIL) databank, an ISO (International Organization for Standardization) 27001 certiﬁed and UK Statistics Authority accredited secure data environment, was granted by the SAIL independent Information Governance Review Panel (Ref: 1421). Findings will be presented at local, national, and international conferences and disseminated by peer-reviewed publication.

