### Objective 1: Effectiveness

We hypothesize that engagement with the VPT will help patients overcome modifiable risks and receive support for vulnerabilities, and that therefore the intervention will reduce the recurrence of unscheduled ED attendance.

Other than those who are most seriously injured, patients will register at ED reception and be triaged, at which point the most appropriate pathway through ED will be determined. At reception patients will be asked about the reason for their attendance, including whether it was due to an assault, data that becomes a part of the Patient Management System (PMS) [39]. Patients may not disclose that the reason for their attendance was assault-related. They might be reluctant, the perpetrator may have accompanied them, or they may wish to avoid scrutiny. One function of the VPTs is to work across clinical teams to improve ascertainment of ARAs. The result is that patients can be stratified according to the extent that they engage with the intervention.

Patients identified in the ED PMS data as having attended due to an assault, but with no further contact with the VPT.Patients identified in the ED PMS or VPT data as having attended due to an assault but did not further engage with the VPT.Patients identified in the ED PMS and VPT data and who engaged with the VPT.

The primary analysis concerns group 3. The reasons for patients not engaging are potentially related to underlying characteristics and in secondary analyses we will explore this. However, it is reasonable to assume that the 3 groups represent varying levels of intervention dose, and therefore secondary analyses and analyses using groups 1-3 will be informative.

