### Allocation

Intervention patients will be identified in the VPT data and will have attended intervention EDs (in Cardiff and Swansea), subject to the above inclusion criteria. Control patients will be identified in the EDDS, and ED attendance was not in an intervention ED.

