##### Exposure Variable

The exposure variable consists of patients engaging with the VPT.

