##### Cost-Effectiveness Analysis Outcomes

For the primary analysis, we will report the incremental cost-effectiveness ratio as the cost per quality-adjusted life-year, the net monetary benefit, and the net health benefit for those being offered versus not offered VPT assessment during their visit to the Accident and Emergency Department. The net monetary benefit and net health benefit will be assessed using a range of values (£15,000-£30,000 [approximately US $20,709-US $41,418, using an exchange rate of 1£≈1.38 US$] per quality-adjusted life year) representing a health decision maker’s willingness-to-pay to obtain the distribution of net benefits at different levels of willingness-to-pay.

For the secondary (multisector) analysis, we report the cost per unit of effectiveness in natural units (eg, cost per reconviction avoided). We will also present the results using the extended impact inventory framework and consider alternative methods of aggregation [64].

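### Objective 3 takes its effect from patients who engage but reports the cost-effectiveness of offering a VPT; the Matching section also misnames the engager effect and misstates its assumption

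*Protocol article*

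**What the plan says.** **Effect estimate (Objective 1).** The Objective 1: Effectiveness section sorts assault attenders into three groups by degree of engagement. It then says "The primary analysis concerns group 3", the patients found in both data sources who engaged. The abstract says "Case patients will be matched to control patients attending EDs without an HVIP", and the Allocation section says "Control patients will be identified in the EDDS, and ED attendance was not in an intervention ED". The Matching section gives the purpose of matching as "to allow derivation of the average treatment effect under the assumption that allocation is not conditional on observed confounders". It names coarsened exact matching, at least 1:1, as the primary method, and aims at a best-matched subset.

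**Engagement.** The Objective 1: Effectiveness section concedes that "The reasons for patients not engaging are potentially related to underlying characteristics and in secondary analyses we will explore this". It adds that "it is reasonable to assume that the 3 groups represent varying levels of intervention dose".

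**Economic contrast (Objective 3).** The Objective 3: Cost-Effectiveness section builds QALYs on engagers compared with non-engagers, and the Exposure Variable section says "The exposure variable consists of patients engaging with the VPT". The Methods subsection of the cost-effectiveness analysis sets the question as offering a VPT or not, both within the study and in the long-term model. The Cost-Effectiveness Analysis Outcomes section reports the ICER, net monetary benefit and net health benefit "for those being offered versus not offered VPT assessment during their visit". The Cost Data section lists engagement among the mediators. The abstract frames the comparison as referral or no referral. Aims and Objectives adds a longer horizon and a national roll-out if an effect is seen.

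**The concern.** Engaging with a service and being offered it are different exposures. An offer reaches people who decline; engagement by definition does not. If the effect is measured in engagers and the economic result is worded per patient offered, the reader is given an answer to a question that was not analysed. The net benefit per patient offered and any roll-out total would then rest on the wrong denominator.

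The Matching section adds to the difficulty. Calling the engager effect the average treatment effect invites its use for everyone eligible. The assumption offered in support would, taken literally, make matching unnecessary: if allocation did not depend on observed confounders, there would be nothing observed to balance. The assumption that carries the weight, no unmeasured confounding given the matching variables, is not the one stated there.

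**Working it through.** **1. The contrasts in Objective 3, side by side.**

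- Abstract: referral versus no referral.
- Objective 3: Cost-Effectiveness, and Exposure Variable: engaging versus not engaging.
- Methods subsection, and Cost-Effectiveness Analysis Outcomes: offering versus not offering.
- Cost Data: engagement is a mediator, which makes sense only if the exposure lies upstream of engagement.

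Engagement cannot be both the exposure and a mediator of that exposure. No step is given that converts an engager effect into an offer effect.

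**2. What the matching estimates.** The treated are group 3, and controls are chosen to resemble them. Weighting the comparison to the treated gives the effect in the treated. Dropping treated patients without a match narrows this to the matched treated. Identification requires that, given the matching variables, being an engaged patient at an intervention ED is independent of the potential outcomes. Controls never received an offer, so would-be engagers cannot be picked out among them, and the plan itself allows that engagement is related to patient characteristics. This is therefore the assumption that needs stating.

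**3. Size of the gap between engaging and being offered.**

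Inputs:

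- Acceptance a = 0.77, from 2312 patients contacted by the Cardiff VPT (Sampling).
- HR in engagers = 0.80, the planning value (Sampling). That value reproduces the plan's 845: Schoenfeld, two-sided 0.05, 90% power, 1:1, gives 4 × (1.960 + 1.282)² / (ln 0.80)² = 844.1, rounded up to 845. The formula counts events.
- HR in decliners, h: not given; varied as an assumption.
- Equal baseline rates in engagers and decliners: not given; an assumption.

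Treating the HR as a rate ratio, offer HR = a × 0.80 + (1 − a) × h = 0.616 + 0.23h.

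| Decliner HR (assumed) | Offer HR | Reduction if offered | 20% ÷ that reduction |
|---|---|---|---|
| 0.7 | 0.616 + 0.161 = 0.777 | 22.3% | 0.90 |
| 0.8 | 0.616 + 0.184 = 0.800 | 20.0% | 1.00 |
| 0.9 | 0.616 + 0.207 = 0.823 | 17.7% | 1.13 |
| 1.0 | 0.616 + 0.230 = 0.846 | 15.4% | 1.30 |

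The engager effect overstates the offer effect only where h exceeds 0.80. At h = 0.7 it understates it.

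**4. The equal-baseline assumption.** The crude one-year reattendance figures in Sampling, 3% in engagers and 23% in non-engagers, cannot support it. Suppose decliners gain nothing. If engagers' untreated risk were 23%, the effect would be −20 points in engagers and 0.77 × −20 = −15.4 points per patient offered. If it were 3%, there would be no effect in either. Those figures do not separate effect from self-selection.

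**The case against.** **Objective 1 asks about involvement.** Aims and Objectives and the Objective 1 hypothesis speak of involvement and engagement, so analysing group 3 answers that question. This stands. A reader might infer that the primary analysis targets the wrong patients; the article does not support that. Secondary analyses of non-engagement and of groups 1 to 3 are also planned.

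**The Matching wording may be loose rather than wrong.** It can be read as saying that allocation no longer depends on observed covariates after matching. That describes what matching achieves, not what must be assumed, so the wording still needs correcting. The correction alone changes no Objective 1 estimate.

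**Overstatement is not certain.** A reader might infer that the engager effect necessarily overstates the effect of offering, by 30%. That figure needs equal baseline rates and no effect at all in decliners. The plan's own dose assumption sits badly with the second condition, since it treats the groups as receiving differing amounts of intervention. The 77% is also acceptance among patients contacted in Cardiff, not Swansea or national uptake. This objection stands, and it is why the size is given as a range.

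**A 30% benefit ratio is not a 30% ICER error.** If intervention and referral costs fall mainly on engagers, moving from engaged to offered dilutes cost and effect together. The ratio then changes mainly through the cost of approaching decliners. This stands too. It does not rescue net benefit per patient offered or roll-out totals, which depend on the denominator.

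**Fuller wording may be in the full protocol.** It may, but the article states the conflicting contrasts outright, so this is not a matter of omitted detail.

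**Conclusion.** The point holds as an internal contradiction in Objective 3 and a misstatement in the Matching section. Effect and exposure come from patients who engage, results are worded for patients offered, and engagement is also called a mediator. The engager effect is an ATT in matched patients, resting on no unmeasured confounding given the matching variables.

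With Cardiff acceptance of 77%, an HR of 0.80 in engagers and equal baseline rates, the relative benefit of offering is overstated by 0%, about 13% or about 30% as the decliner HR goes from 0.8 to 0.9 to 1.0. The direction is the expected one under the plan's benefit hypothesis and dose assumption, but it is not guaranteed. If decliners have a higher untreated rate than engagers, the offer HR moves closer to the decliner HR. The documents do not fix the size of any change in the ICER, because they do not settle over which patients costs are counted. They do not show that the Objective 1 comparison is itself misdirected.

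**What to change.** 1. **Matching section:** name the Objective 1 estimand as the effect in matched engaged patients (ATT). State the assumption as independence of allocation and potential outcomes given the listed matching variables.
2. **Objective 3:** use one contrast throughout. For the offered-versus-not-offered ICER, net benefit and roll-out, compare all patients with a documented VPT contact or offer, engaged or not, with matched controls, and count both costs and effects over that same group. Alternatively, keep the engager analysis and relabel the ICER as engaged versus not engaged, without carrying it to an offer or a roll-out.
3. **Cost Data and Exposure Variable:** decide whether engagement is exposure or mediator, and say so once.

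The offered group should be defined by documented contact rather than as groups 2 and 3 combined, because group 2 can include patients known only from the hospital system with no recorded offer. Multiplying the engager effect by uptake is not a substitute: it presumes no effect in decliners, and applied to a hazard ratio it fails outright (0.77 × 0.80 = 0.616 would enlarge the benefit). The all-contacted contrast removes selection by engagement but not selection into being contacted, which should be stated as a limit.

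Cost: a few sentences and one contrast re-run on data the study already holds, since the VPT records extent of engagement. The reported benefit may become smaller. The Results section says the Objective 1 and Objective 3 analyses are complete, with release expected in June and August 2026, so the re-run should be declared as a later change.

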##### Missing Data

Missing data may arise specific to the use of census data, where it is feasible that records are missing entirely or patients did not disclose personal characteristics. However, given that these characteristics are recorded across multiple datasets, the expectation is that missingness will minimally impact the analyses. Nevertheless, missingness will be considered should it arise in the process of analysis.

#### Objective 2: Ascertainment

The hypothesis is that a violence attendance is more likely to be ascertained as such with the additional VPT resource present in ED. All unplanned attendances can be coded as ARA or not (1, 0). The time series begins in January 2012, and the 2 sites (Cardiff and Swansea) can be individually compared with all other Type I EDs in Wales. This indicates that a difference-in-difference model [59] is appropriate. We will analyze Cardiff first, using the implementation in Swansea as a future replication of the intervention to facilitate a more robust causal interpretation of any effect. Additional descriptive analysis can explore patient groups (age, gender, and time of attendance) more likely to be ascertained by the VPTs. Unlike Objective 1, we are interested in all ED attendances, as the opportunity to provision safeguarding is applicable across all ED attendances, irrespective of the frequency of attendance.

#### Objective 3: Cost-Effectiveness Analysis

The aim of the economic evaluation is to understand the costs and consequences of providing a VPT versus no VPT within EDs. For this study, we will focus on the objectives of understanding whether the VPT represents value for money from an NHS perspective.

##### Methods

A within-study analysis will determine the short-term cost-effectiveness of offering VPT relative to not offering VPT within EDs. Estimates derived from this study will be used to inform a long-term decision analytic model examining the cost-effectiveness of providing, versus not providing, VPT within EDs over a longer time horizon. Alternative perspectives for the analysis will be considered, with the NHS perspective being the base case. Cost-effectiveness will be presented using standard statistics.

##### Exposure Variable

The exposure variable consists of patients engaging with the VPT.

##### Outcome Variables

Health-related outcome variables include improved mental health outcomes, measured as a reduction in primary and secondary care visits for a mental health reason, reduced substance use, improved physical health, measured as a reduction in ARAs in ED, and improved health-related quality of life (HRQoL), measured using injury-related estimates from the literature. Data on all outcomes will be sourced from the SAIL databank [43]. Estimates will be measured on a quarterly basis for the follow-up period (12-48 months). HRQoL will be estimated using the literature, in line with other studies on hospital-based violence prevention programs.

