### Intervention as Implemented

Since November 2019, a collaborative VPT between the police and NHS has been operational in a South Wales Type I (consultant-led with resus) ED in Cardiff (the capital and largest city in Wales), and a second VPT began in an adjacent South Wales Type I ED in Swansea (the second-largest city in Wales) in January 2022. The VPTs initially sought to identify patients attending the ED due to violence. This remit was broadened, with VPTs subsequently receiving referrals from across the hospital and other community health care teams (eg, Minor Injury Units [MIUs] and General Practitioners).

The VPTs work with patients to gain an understanding of any circumstances contributing to their exposure to violence. They refer patients into care pathways (primary, secondary, and tertiary care, or third-sector organizations) to address any vulnerabilities or modifiable risks and can work alongside the third sector (nonprofit and charitable enterprise) to provide continual case management. The VPTs also train other staff within the hospital to improve the identification of violence-related injury, to support clinical staff interactions with patients, and to maintain safeguarding procedures. In addition, the EDs at Cardiff and Swansea take part in information sharing to tackle violence, in which anonymous data and intelligence regarding violent incidents are shared with community safety partnerships. These anonymized data enable partner resources to be best used for violence prevention, part of the Cardiff Model for violence prevention [39]. Following implementation, both VPTs expanded the age range of patients to encompass all age groups.

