### Objective 2: Ascertainment

Our second hypothesis is that intervention implementation improves ARA ascertainment.

Patients attending ED can do so repeatedly within periods of time. This frequency is likely associated with the modifiable risks associated with ARA and is of interest here. For Objective 2 it is therefore appropriate to determine the proportion of attendances identified as violence related. This generates time-series data. The outcome of interest is therefore the count of ARAs across all EDs. ARA attendance is defined as ARA in the ED PMS or, in the case of intervention sites, in the ED, PMS, or VPT data. Codes indicating the Provider Site (the ED in its hospital) are available in the EDDS, and this allows comparison between intervention EDs and control EDs. While intervention EDs have been in continual service since before the time-series start dates, this is not so for all Type I EDs in Wales; there have been several changes, with some EDs closing and others opening or being modified to receive additional patients. This, coupled with the intervention sites located at two of the largest hospitals in Wales, reduces the scope for selecting matching control sites [40], leading to potentially important baseline differences in the interrupted time-series data [41]. The counterfactual will therefore be ARAs across all control Type I EDs.

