### Objective 3: Cost-Effectiveness

We aim to determine whether the VPT represents value for money. The primary outcome will be quality-adjusted life years, which will be estimated based on effectiveness estimates comparing ED attendance, reattendance, and any injuries received for those engaging in the VPT service relative to those who do not. Costs will be captured from an NHS perspective, reflecting the cost of the intervention but also other costs to the NHS due to referral. A secondary cost-effectiveness analysis will undertake a societal perspective, which will explore additional costs across social care, the police, and the third sector.

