##### Covariates of Interest

The following covariates will be included within the fixed effects panel regression model, patient age, gender, severity of injury, number of years the VPT has been operating, year, and quarter. Referral uptake will be treated as a mediating variable and not adjusted for in the models.

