##### Resource Use

Health care resource use will include number and type of visits with

primary care (eg, General Practitioner),secondary care (eg, inpatient stays and outpatient clinic appointments), andother services (eg, other health care professional visits, physiotherapy, occupational therapy, mental health therapy, and drug and alcohol treatment).

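### Two Objective 3 benefit measures, mental-health visits and coded assault attendances, are biased against a working VPT and can reverse sign

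*Protocol article*

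**What the plan says.** Outcome Variables, under the Objective 3 cost-effectiveness analysis, fixes both the measures and the direction in which they are scored. Mental health is to be judged as "improved mental health outcomes, measured as a reduction in primary and secondary care visits for a mental health reason" and physical health as "improved physical health, measured as a reduction in ARAs in ED". Both are measured quarterly over 12 to 48 months from SAIL data.

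Four other places bear on how these measures behave:

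- Intervention as Implemented describes what the VPTs do: "They refer patients into care pathways (primary, secondary, and tertiary care, or third-sector organizations) to address any vulnerabilities or modifiable risks".
- Covariates of Interest states: "Referral uptake will be treated as a mediating variable and not adjusted for in the models".
- Objective 3: Cost-Effectiveness takes an NHS cost perspective, "reflecting the cost of the intervention but also other costs to the NHS due to referral". Resource Use lists among the services to be counted "physiotherapy, occupational therapy, mental health therapy, and drug and alcohol treatment".
- Objective 2: Ascertainment, in the design section, states: "Our second hypothesis is that intervention implementation improves ARA ascertainment". The analytic section for the same objective repeats it: "The hypothesis is that a violence attendance is more likely to be ascertained as such with the additional VPT resource present in ED". The ARA definition given there adds VPT records as a source at intervention sites only.

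**The concern.** An outcome scored as benefit should not be pushed towards harm by the intervention's own working parts. Here two are.

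A patient whose unmet mental-health need is found and referred will, if the referral succeeds, make more mental-health visits. The scoring rule reads that as deterioration. The same contacts are also charged as NHS cost, which is right in itself, but the programme is then marked down twice for one success.

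A VPT that helps staff recognise violence will cause more of the same violent attendances to be coded as ARA. The scoring rule reads that as worse physical health.

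At stake is whether the reported Objective 3 outcomes could show no benefit, or apparent harm, from a programme that does what it is meant to do.

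**Working it through.** **Plan figures.** The protocol gives no expected size for referral-generated visits, for the ascertainment gain, or for the effect on either measure. The one design figure that can be recomputed is the total of 845 in Sampling. A two-sided Schoenfeld calculation at a hazard ratio of 0.8, alpha 0.05 and 90% power gives 844.1, rounded up to 845. This point does not depend on it. Only the ratio of 0.8 is borrowed below, as a stand-in for a true effect.

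**Mental-health visits.** The steps are:

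1. The VPT refers into primary and secondary care. The measure counts primary and secondary care visits.
2. Usual Care says that control EDs have no processes to support referral to outside agencies, so referral-generated visits will tend to differ between groups.
3. Referral uptake is a mediator left out of the models, so those visits stay in the effect estimate.
4. An increase in visits is scored as worse health.

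The protocol does not say outright that referrals include mental-health care. That is an inference, but a close one: Theoretical Framework names mental health status among the characteristics linked to violence, and Resource Use lists mental health therapy.

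If need-driven visits fall by an assumed 20% from a baseline of m visits per patient-year, the fall is 0.2 × m. That many extra referral visits per patient-year cancel it.

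| Assumed baseline m | Extra referral visits that cancel a 20% fall |
|---|---|
| 0.25 | 0.05 |
| 0.5 | 0.1 |
| 1 | 0.2 |
| 2 | 0.4 |

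At one visit a year, one extra visit for every five patients is enough to cancel the benefit. Anything above that reverses the sign.

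**Coded ARAs.** When the comparator is seen at EDs without a VPT:

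coded ratio = true ratio × ascertainment ratio

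The ascertainment ratio is the probability that a violent attendance is coded as ARA with a VPT, divided by that probability without one.

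| Assumed ascertainment ratio | Coded ratio at a true ratio of 0.8 |
|---|---|
| 1.00 | 0.80 |
| 1.10 | 0.88 |
| 1.25 | 1.00 |
| 1.50 | 1.20 |
| 2.00 | 1.60 |

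The share of the 20% benefit hidden is (coded ratio − 0.8) / 0.2. At 1.10 this is 0.08 / 0.2 = 40%. Half is hidden at 1.125, since 0.8 × 1.125 = 0.90. The sign reverses only above 1 / 0.8 = 1.25, for example if ascertainment rises from 60% to more than 75%. It cannot reverse if baseline ascertainment is already 80% or more, because 0.80 × 1.25 = 1.

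With the early Cardiff contrast in Sampling (3% against 23%, ratio 3/23 = 0.13) used as the true ratio, the coded ratio is only 0.26 even if ascertainment doubles, so there is no reversal.

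**Is there a correction elsewhere?** The Objective 3 methods, statistical analysis and covariate sections give none for either mechanism. Objective 1 avoids the coding problem because it counts all unplanned ED attendances, whether or not they are coded as assault.

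**The case against.** The strongest case on the other side has four parts.

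**Direction.** A reader might infer that both measures will move the wrong way whenever the VPT works. The documents do not support that. They give no size for either mechanism, and over 12 to 48 months visits could rise first and fall later. What stands is a bias against the VPT that may or may not be large enough to reverse the sign.

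**QALY and ICER.** A reader might infer that both measures corrupt the cost per QALY. Objective 3: Cost-Effectiveness bases QALYs on ED attendance, reattendance and injuries. Quality of life comes from injury-related literature values, and the primary Markov model has likely states of healthy, injured and dead. No section feeds mental-health visits into the QALY, and counting them as cost is correct. Coded ARAs matter to the ICER only if they define or inform injury, which the text does not settle. This limits the consequence considerably.

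**Comparator.** Objective 3: Cost-Effectiveness and Exposure Variable read as engaged against not engaged. The Methods and Cost-Effectiveness Analysis Outcomes sections of the economic evaluation read as offered against not offered. If non-engagers attend the same EDs, both groups face largely the same coding. Nor does Outcome Variables say that the Objective 2 ARA definition carries over. Using ED system coding alone would not fully remove the problem, however, because the VPTs also train hospital staff to identify violence.

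**Model.** The panel model has individual fixed effects and terms for year, quarter and years of VPT operation. These may absorb part of an ascertainment shift. They do not clearly remove it, because detection changes when the exposure begins.

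The substance-use outcome might be thought to share the fault. It would if it were read from the substance misuse treatment dataset, but the protocol does not assign a source to it.

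**Conclusion.** The point holds as a bias in two reported outcomes. The mental-health measure is the clearer case: referral is a core activity, its effect is left in the estimate, and an increase is scored as harm. An assumed 20% fall is cancelled by 0.05 to 0.4 extra visits per patient-year at assumed baselines of 0.25 to 2.

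The ARA measure is biased where comparators are seen at EDs without a VPT. At an assumed true ratio of 0.8, the coded ratio is 0.88, 1.00 and 1.20 for assumed ascertainment ratios of 1.10, 1.25 and 1.50. Reversal therefore needs a gain of more than 25%.

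These sizes rest on assumed inputs and on no absorption by the model. An effect on the QALY and ICER is conditional on coded ARAs informing the injury inputs. This should be corrected, but it does not undermine the Objective 1 primary outcome.

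**What to change.** 1. Treat scheduled mental-health contacts as referral uptake and as cost, not as a health outcome. Do the same for substance-misuse treatment contacts if those are the measure of substance use.
2. Score mental health by unscheduled events, such as emergency admissions for mental health or self-harm in the inpatient data (PEDW).
3. Score physical health, and any injury input to the QALY, by all unplanned injury attendances or emergency injury admissions.
4. Keep coded ARAs as a sensitivity analysis, with the same ED-system-only definition in both arms and a range of ascertainment ratios. Results reports that the Objective 2 analyses are complete and published, so an estimate to centre that range may already exist.
5. State the Objective 3 comparator once, since the size of the coding bias depends on it.

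The cost is modest. The ED and inpatient datasets are already in the project, although the article does not describe the fields that would identify injury or self-harm, and these need to be confirmed. An all-injury outcome is less specific to violence and so will dilute a violence-specific effect. Because Results gives Objective 3 as completed in January 2026, the re-analysis must be disclosed and labelled post hoc, with the planned measures reported beside it.
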